#### 11.2.2. Methods

##### Phase 1: Pilot Study (8 Months)

The team will further refine the VRG educational programme based on the results and feedback from our previous pre–post intervention study. Then, two schools will be invited to participate in the pilot study. Training in student recruitment will be provided to the teachers. The recruited schoolchildren will participate in the VRG educational programme, which will be delivered by the researchers, for 6 months. Parents will also receive training in the assessment of their children’s hand-hygiene practices and collection of throat gargle samples at home. Feedback will be collected before (T1) and immediately after the intervention (T2) from the teachers, parents and schoolchildren on the feasibility of subject recruitment, the understandability of hygiene practice assessment and the attractiveness and learnability of the VRG design. The intervention protocol will be refined according to the feedback collected from community stakeholders (schools, schoolchildren and parents).

To study the cost-effectiveness of the VRG, the VRG will be implemented in one group of 60 students and conventional educational programme will be implemented in another group of 60 students. The total costs spent on both groups will be calculated, these include material production, human resources, facilities and equipment for programme implementation. The effectiveness of the VRG and conventional education programme will be measured as the number of students demonstrating compliance to hand hygiene practice. The ratio of cost per unit of effectiveness can be calculated by dividing the total cost with the number of students demonstrating hand hygiene compliance. The ratio will be compared between the VRG programme and conventional education programme.

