##### Hand-Hygiene Compliance (T1, T2, T3 and T4)

A hand-hygiene compliance checklist [59] will be used to measure the extent of hand-hygiene compliance in the intervention and control groups. Higher scores indicate better performance.

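### Study 5's pilot cost-effectiveness analysis compares average cost per compliant student, which does not give the cost per additional compliant student and makes no stated allowance for baseline compliance

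*Protocol article*

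**What the plan says.** The method is set out in the protocol article, section 11.2.2, Phase 1: Pilot Study.

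- **Groups:** the VRG is given to "one group of 60 students and conventional educational programme will be implemented in another group of 60 students".
- **Costs:** "The total costs spent on both groups will be calculated"; "these include material production, human resources, facilities and equipment for programme implementation". No amounts are given.
- **Effect:** effectiveness "will be measured as the number of students demonstrating compliance to hand hygiene practice".
- **Ratio:** obtained "by dividing the total cost with the number of students demonstrating hand hygiene compliance".
- **Comparison:** "The ratio will be compared between the VRG programme and conventional education programme".

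The article mentions no difference in cost, no difference in effect and no change from baseline for this analysis, and no other section describes a different cost-effectiveness method.

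**The concern.** The stated purpose is to study the cost-effectiveness of the VRG, and a conventional programme is run beside it for that purpose. The question is therefore comparative: if a school moves from conventional education to the VRG, how much more does it spend and how many more students become compliant? Two separate averages do not answer this. Each spreads a programme's whole cost over all its compliant students, so the price of the extra compliance does not appear.

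A second weakness lies in the denominator. Neither group in this comparison goes without a programme. Dividing all the cost by all compliant students treats compliance without a programme as zero. If some students wash their hands properly beforehand, the same number is in effect added to both counts. That pulls the ratio of the counts towards 1 and makes the more effective programme look relatively worse.

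At stake is the message to schools from the only cost-effectiveness analysis described for Study 5. The main trial's conclusions are not at stake.

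**Working it through.** The article gives no costs, compliance rates or cost-effectiveness result, so there is no figure to reproduce. The stated method can be tested algebraically and over assumed values.

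**Notation.** C_V and C_C are the total costs of VRG and conventional education; E_V and E_C are the numbers compliant out of 60; B is the number compliant beforehand, taken as equal in the two groups.

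**Formulas.**

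1. Stated ratio: C/E in each group. VRG has the lower average if C_V/C_C < E_V/E_C.
2. Incremental ratio: (C_V − C_C)/(E_V − E_C).
3. Baseline-corrected average, used here only as a diagnostic: C/(E − B). VRG has the lower value if C_V/C_C < (E_V − B)/(E_C − B).

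When E_V > E_C > B > 0, (E_V − B)/(E_C − B) exceeds E_V/E_C. Leaving B in therefore always works against whichever programme has more compliant students.

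**Inputs.** The 60 per group is from the article. Everything else is assumed: E_C = 36, E_V = 48, B from 0 to 30, and cost ratios of 1.2 to 3.

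**Break-even cost ratios.**

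| B (of 60) | Stated average: 48/36 | Baseline-corrected: (48 − B)/(36 − B) |
|---|---|---|
| 0 | 1.33 | 48/36 = 1.33 |
| 12 | 1.33 | 36/24 = 1.50 |
| 18 | 1.33 | 30/18 = 1.67 |
| 24 | 1.33 | 24/12 = 2.00 |
| 30 | 1.33 | 18/6 = 3.00 |

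For cost ratios between the two columns, the ranking differs. Outside that window, and at B = 0, it does not.

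Other assumed pairs behave in the same way:

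- 36 v 54: stated break-even 54/36 = 1.50; corrected 42/24 = 1.75 (B = 12) to 24/6 = 4.0 (B = 30).
- 42 v 54: stated break-even 54/42 = 1.29; corrected 42/30 = 1.40 (B = 12) to 24/12 = 2.0 (B = 30).

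**One worked case** (B = 24, C_C = 6,000, C_V = 9,000, cost ratio 1.5):

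- Stated averages: 6,000/36 = 167 and 9,000/48 = 188, so conventional looks better.
- Baseline-corrected averages: 6,000/12 = 500 and 9,000/24 = 375, so VRG looks better.
- Incremental: 3,000/12 = 250 per additional compliant student.

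**The averages hide the incremental figure even when the baseline is zero.**

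- 36 v 54 at a cost ratio of 3: averages 6,000/36 = 167 and 18,000/54 = 333; incremental 12,000/18 = 667.
- 36 v 48 at a cost ratio of 1.2: averages 167 and 7,200/48 = 150; incremental 1,200/12 = 100.

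The incremental cost can thus lie above or below both averages and cannot be read from comparing them.

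**Effect of the baseline on the incremental ratio.** (E_V − B) − (E_C − B) = E_V − E_C, so an equal baseline cancels. If the groups differ at baseline, a change score or an adjustment is needed as well.

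**The case against.** The strongest reply is that this is a side analysis. Cost-effectiveness is not among Study 5's four objectives (section 11.1) or its listed outcomes (section 11.2.4), and the stop-and-go criteria in section 12 do not depend on it. The article says the ratios will be compared, but not that the lower one wins. Cost per compliant student is a legitimate descriptive figure, and anyone holding the totals and counts can derive the incremental ratio. All of this stands and limits the weight of the point. It does not remove it: the article fixes the comparison it will make, and that comparison does not address its stated purpose.

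A reader might infer three stronger things that the documents do not support.

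- **That the analysis will pick the wrong programme, or is biased towards conventional education.** No costs or compliance rates are given. The reversal needs a positive baseline and a cost ratio within a window. If VRG's cost ratio is below its effect ratio, the averages already favour VRG. Nor does an incremental ratio show which programme is preferable without a value for an extra compliant student, and the article gives none.
- **That the article says students compliant at baseline are credited to the programme.** It does not. This follows from a raw count with no date and no subtraction.
- **That baseline data are certainly available in the pilot.** In the pilot text, T1 and T2 are tied to feedback. The compliance checklist headed T1 to T4 (section 11.2.4) "will be used to measure the extent of hand-hygiene compliance in the intervention and control groups", and the four time points belong to the main design (section 11.2.3).

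It is also fair to object to elaborate uncertainty analysis. Costs are group totals and the pilot invites two schools, so student-level resampling would ignore clustering and suggest precision that is not there.

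**Conclusion.** The point holds in a limited form. The article commits Study 5's pilot to comparing average cost per compliant student, which does not give the cost per additional compliant student. Because the count carries no stated allowance for prior compliance, the comparison of averages can rank the programmes differently from a baseline-corrected one.

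The size is conditional. With 36/60 and 48/60 compliant, the disagreement runs from a cost ratio of 1.33 up to 1.5 for a baseline of 12, and up to 3.0 for a baseline of 30; it vanishes at a baseline of 0. These compliance counts and baselines are assumptions, as are equal baselines and the premise that, without a programme, compliance would stay at its baseline level. The failure to give an incremental figure needs none of these assumptions.

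This is a secondary pilot analysis. The main-trial sample size and primary outcomes are unaffected.

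**What to change.** In section 11.2.2, Phase 1, make the cost-effectiveness result three reported quantities: the difference in total cost (VRG minus conventional), the difference in the number or proportion compliant, and their ratio as the incremental cost per additional compliant student. Keep the average ratio of each programme as description only.

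State whether compliance is recorded before the programme in the pilot. If it is, use the change from baseline or adjust for it. If it is not, report the follow-up difference and say that it assumes similar compliance in the two groups at the start.

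Label the result exploratory, because only two schools take part and costs are group totals.

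The core change uses totals and counts already planned, so it costs only analysis wording. The baseline step is equally cheap if pre-programme compliance is already collected; otherwise it would need one extra measurement, and the incremental ratio can be reported without it.

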##### Phase 2: Main Study (40 Months)

Intervention group: Educational intervention using a VRG over 3 weeks.

The schoolchildren in the intervention group will take part in an innovative VRG-based educational programme featuring: (1) Web-based health education on (i) SARS-CoV-2 transmission, (ii) proper hand and respiratory hygiene practices and (iii) the importance of community SARS-CoV-2 screening and throat-gargle collection procedures; (2) built-in instant feedback on their performance of hygiene practices; and (3) a chat function for efficient nurse–parent–schoolchild interactivity and communication. The schoolchildren will receive three sessions (one per week) of the VRG-based educational programme, which will be provided by the research team during extracurricular activity time. Each session will consist of two VRGs and will last 30–45 min. Six VRGs will be designed, representing six ascending levels. After completing each level, schoolchildren will be granted access to the next level. This design will engage the schoolchildren in playing the VRGs. Levels 1 and 2 will address the fundamentals of SARS-CoV-2 transmission and hand hygiene; levels 3 and 4 will consist of family-based scenarios exemplifying the chain of infection and throat gargle collection; and levels 5 and 6 will address how to combat germs in school-based scenarios and the importance of community SARS-CoV-2 screening. The schoolchildren will be required to complete electronic questionnaires pre-post and 3 months and 6 months after they participate in the educational programme. Parents will use the online checklist provided to assess schoolchildren’s performance on the return-demonstration of hand hygiene and throat gargle pre–post, and 3 months and 6 months after the educational programme. To ensure the accuracy of the recordings of the schoolchildren’s hygiene practices, the return-demonstration will be video-recorded and uploaded to the online platform by parents, for analysis by the research team.

Control group. The schoolchildren in this group will receive the usual health education or care available in the community. The VRG equipment will not be made available to the schoolchildren in this group within the intervention period.

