### 11.2. Plan of Investigation

This will be a single-blinded, cluster RCT with two-armed repeated measures.

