#### 11.2.1. Subjects

Primary schoolchildren will be recruited from local primary schools. The eligibility criteria will be (1) primary school children aged 6–12, and (2) able to communicate in Chinese and to read Chinese. The exclusion criteria will be (1) reported mental or physical health disorders and (2) engagement in other health educational programmes related to hygiene practices 2 months or less before recruitment. The school management staff will help us to liaise with the schoolchildren and refer them to the research team. Informed consent will be obtained from school principals, parents and schoolchildren before the study begins. To minimise selection bias, the children will not be informed of whether they will join the intervention group or the control group. Potential subjects will be screened and recruited in these schools by the research team. In order to avoid data contamination in the control group, school children who have siblings in the intervention group will not be recruited. Details of the study will be provided to the schools, the schoolchildren and their parents. Sample size has been computed to obtain a statistical power of no less than 0.8 to detect the significance of the four objectives with continuous outcomes at a 0.05 level of significance. With 0.2 as the Cohen’s d effect size and under balanced allocations, we have set the intra-cluster correlation to 0.05, the correlation among level-2 units nested in a cluster to 0.01, the number of level-1 units to 30, and the sample size of level-2 stratified units to 2, we have 18 school clusters in each arm. Therefore, the sample size should be 2160.

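### Study 5: parents who will almost certainly know the arm score the hand-hygiene practice checklist, and no masked assessor is named

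*Protocol article*

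**What the plan says.** Section 11.2 labels the trial: "This will be a single-blinded, cluster RCT with two-armed repeated measures". It does not say who is blinded. The only concealment described is in 11.2.1, where "the children will not be informed of whether they will join the intervention group or the control group", and the reason given is selection bias. The same section says: "Details of the study will be provided to the schools, the schoolchildren and their parents".

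Section 11.2.2, Phase 2, assigns the rating: "Parents will use the online checklist provided to assess schoolchildren’s performance on the return-demonstration of hand hygiene". The ratings, which also cover the throat gargle, are made before and after the programme and at 3 and 6 months. To check accuracy, "the return-demonstration will be video-recorded and uploaded to the online platform by parents, for analysis by the research team". The intervention programme includes "a chat function for efficient nurse–parent–schoolchild interactivity and communication", and its sessions are ones "which will be provided by the research team during extracurricular activity time". For controls: "The VRG equipment will not be made available to the schoolchildren in this group within the intervention period".

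On instruments, 11.2.4 says the online checklist records hygiene practice and gargle performance, and gives hand-hygiene compliance to the children's e-questionnaire. The Hand-Hygiene Compliance paragraph then measures compliance by a checklist in both arms and names no rater. Section 11.2.5 lists knowledge and practice, hand bacterial load and respiratory-virus detection as primary outcomes.

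**The concern.** A checklist rating of a demonstrated skill involves judgement, and the person named to make it is the child's own parent. In the intervention arm that parent has received study details, can use the programme's chat and has a child attending three weekly virtual reality sessions. Masking that parent is not realistic.

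If involvement in the programme makes intervention parents score more generously after baseline than control parents do, the practice outcome shows a difference even when hand-washing has not changed. A larger sample does not remove this. The trial is sized for a small effect (d = 0.2), so a modest rating shift is enough to matter. Readers may also take the single-blind label to mean that outcome assessment is protected, and the text does not show that it is.

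**Working it through.** **Who rates, who checks, who is masked**

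| Step | Who | Knowledge of arm |
|---|---|---|
| Checklist score | Parent (11.2.2) | Not stated; almost certain in the intervention arm |
| Recording and upload | Parent (11.2.2) | As above |
| Video analysis | Research team (11.2.2) | Masking not stated |
| Delivery of sessions | Research team (11.2.2) | Known |
| Blinded party | Not named (11.2) | – |

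**Inputs, all from 11.2.1:** d = 0.2; alpha 0.05; power at least 0.80; 30 children in each of 2 grade strata per school; correlations 0.05 and 0.01; 18 schools per arm. Sidedness is not stated, but two-sided reproduces the plan's figure (one-sided would need 14.2, so 15 schools).

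**Reproducing the plan's figure**

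- Design effect = 1 + (30 − 1) × 0.05 + 30 × (2 − 1) × 0.01 = 1 + 1.45 + 0.30 = 2.75.
- Schools per arm = 2 × (1.960 + 0.842)² × 2.75 / (0.2² × 60) = 17.99, rounded up to 18.
- Total = 18 × 2 × 60 = 2160, as stated.

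**Sensitivity to a rating shift**

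- Children per arm = 18 × 60 = 1080; effective number = 1080 / 2.75 = 392.7.
- SE of the standardised difference = √(2 / 392.7) = 0.0714.
- Smallest significant observed difference = 1.96 × 0.0714 = 0.14 SD.
- With no true effect and a between-arm shift b, the chance of significance is Φ(b/SE − 1.96) + Φ(−b/SE − 1.96).

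| Assumed shift b (SD) | b/SE | Chance of a significant result |
|---|---|---|
| 0 | 0 | 5% |
| 0.05 | 0.70 | 11% |
| 0.10 | 1.40 | 29% |
| 0.20 | 2.80 | 80% |

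The documents give no value for b, so these shifts are assumptions. The calculation uses one cross-sectional comparison, whereas 11.2.5 compares change over time. In that analysis leniency already present at baseline cancels, so b means only the part that appears later and differs by arm.

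**The case against.** The strongest objection is that the text does not establish the parent score as the primary practice measure. Sections 11.2.2, 11.2.4 and 11.2.5 leave three candidates: the parent's checklist, the team's video score and the e-questionnaire. This stands. It limits the point to an exposure under the plan as written, and it is why the instrument has to be settled first.

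Second, a condensed article may leave the identity of the masked party to the full protocol, and a masked reader within the research team is not excluded. This also stands in part. However, the article does name the rater, and that rater is someone who cannot plausibly be masked.

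Third, the central video analysis is already a safeguard. It is, but it is described as a check on accuracy, and nothing says whether it overrides the parent's score.

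A reader might infer more than the documents support:

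- That the whole trial can be positive through rater knowledge alone. Bacterial counts, RT-PCR and the true/false knowledge test are not scored by parents.
- That the people who deliver sessions also score the videos. The article uses one collective term for both tasks and does not identify individuals.
- That keeping children unaware of their group is the trial's blinding and must fail. Its stated purpose is to limit selection bias at recruitment.
- That any parental leniency biases the result. Parents are the named raters and only a difference between arms matters, so equal leniency in both arms does no such harm.

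**Conclusion.** The point holds in limited form. As written, the plan has the practice checklist scored by parents, and those in the intervention arm will almost certainly know the arm. It states no masking of the video review and does not say which score is analysed as primary. Parental knowledge of the arm is an inference from the study information, the chat function and the visible programme; no sentence says that parents are told the allocation.

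The exposure concerns one of several primary outcomes, plus gargle performance. The percentages illustrate sensitivity and do not estimate the bias to expect. Their message is that a trial able to call 0.14 SD significant has little tolerance for a differential rating shift of similar size. The remedy is inexpensive and belongs before data collection, because no later analysis can restore masked rating.

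**What to change.** 1. Reconcile 11.2.2, 11.2.4 (including the Hand-Hygiene Compliance paragraph) and 11.2.5 on which instrument and which rater give the primary practice score.
2. Make that score the research team's checklist rating of the uploaded videos in both arms. State that videos are collected in controls too, since the video step is described only in the intervention-group text.
3. Have the videos read under coded ID without knowledge of arm, and where feasible of time point, by existing team members who deliver no sessions.
4. Keep the parent score as a supportive measure.
5. In 11.2, name the masked assessor as the blinded party.

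The sample size does not change, and the team is already committed to analysing the videos. The costs are these:

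- Unusable or missing videos become missing data for a primary outcome.
- Coding and ordering the files takes effort. At full follow-up there are up to 2160 × 4 = 8640 hand-hygiene demonstrations, and mixing time points means holding files until later visits are in.
- If control videos are not currently planned, collecting them is extra work.
- Parents still control the recording, so the bias is reduced, not removed.

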#### 11.2.3. Study Design

The duration of each schoolchild’s involvement in the study will be 6 months, with assessments at baseline before the intervention (T1), immediately after the intervention (T2), at 3 months after the intervention (T3), and at 6 months after the intervention (T4). It is proposed that 12 schools will participate in the study every 12 months, and thus it will take 36 months to complete the intervention in 36 schools. Four months will be used for data cleaning, analysis and report writing. Data will be collected at four time-points, T1, T2, T3 and T4, to test the sustained intervention effect.

Randomisation: A large-scale stratified cluster RCT will be undertaken. Primary schoolchildren will be recruited via local conventional school clusters from 18 districts in Hong Kong, which have been chosen to provide a geographically representative sample. The cluster sizes will be equal across school clusters. We will select 36 primary schools and will randomly assign them to the intervention group or the control group in a ratio of 1:1. To adjust for age as a confounding factor, the schoolchildren from each school cluster will be separately drawn from lower grades (Primary 1 to 3) and higher grades (Primary 4–6). Therefore, we have designed a three-level hierarchical mixed model that is randomised at the third level. Here, a school is considered to be a level-3 cluster, the grades within a school are considered to be level-2 stratified units and the schoolchildren in our trials are considered as level-1 units [58].

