#### 11.2.5. Data Analysis

Descriptive statistics will be used to present all of the demographic, programme attendance and outcome data. Chi-square or independent sample *t*-tests (for categorical and interval data, respectively) will be used to identify the heterogeneity of demographic and baseline data in the two groups and settings. The effectiveness of the VRG-based educational intervention on the primary outcomes (the level of knowledge and practice, the bacterial loads and the detection rates of respiratory viruses) will be examined by linear mixed-effect modelling to compare changes in the primary outcome values of the intervention and control groups over time (from baseline to the two post-tests) on an intention-to-treat basis, using repeated-measures analysis of covariance, multivariate analysis of covariance and/or mixed modelling techniques.

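### Study 5: the two grade bands sampled in every school should enter the outcome models as a fixed effect; as a random level-2 unit alone they can inflate the standard error

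*Protocol article*

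**What the plan says.** Section 11.2.3 (Study Design, Randomisation) allocates 36 schools 1:1. It draws children separately from Primary 1 to 3 and Primary 4 to 6 in every school and gives adjustment for age as the reason. From this it derives a three-level mixed model randomised at the school level, in which "the grades within a school are considered to be level-2 stratified units".

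Section 11.2.1 (Subjects) sizes the trial on the same hierarchy. "Sample size has been computed to obtain a statistical power of no less than 0.8", at a 0.05 level. The inputs are a standardised effect of 0.2 with equal arms, an intra-cluster correlation of 0.05, 30 children per level-2 unit and two such units per school. For grades within a school it sets "the correlation among level-2 units nested in a cluster to 0.01". The result is 18 schools per arm and 2160 children.

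Section 11.2.5 (Data Analysis) says that the primary outcomes "will be examined by linear mixed-effect modelling to compare changes in the primary outcome values of the intervention and control groups over time". It allows repeated-measures or multivariate analysis of covariance and/or mixed models, and lists no covariates. Section 11.1 (Aims) words the objectives as comparisons at 6 months after the intervention.

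**The concern.** Lower and higher grades are the same two categories in all 36 schools. They form a fixed factor crossed with school, probably with a systematic difference in outcome. They are not two exchangeable units sampled at random within each school. Section 11.2.3 presents the level-2 placement as the consequence of wanting to adjust for age, but a random effect for grade-within-school does not model a systematic gap between the bands. Separate sampling balances age between the arms; it does not put age into the model.

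An analyst who follows the text literally could fit random effects for school and grade-within-school and no grade-band term. The gap would then be absorbed into the level-2 variance, for which the sizing correlations of 0.05 and 0.01 leave no room. What is at stake is precision: a real effect of 0.2 SD could be missed because the reported standard error is too large.

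**Working it through.** **Inputs from Section 11.2.1.** d = 0.2; correlation within a grade band of a school 0.05; correlation across bands of a school 0.01; 30 children per band; 2 bands; 18 schools per arm. The variance components, with total 1, follow: school 0.01, grade-within-school 0.05 − 0.01 = 0.04, child 0.95. **Assumptions:** a two-sided test (not stated for Study 5) and the lower-higher gap g, for which the documents give no figure.

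**Step 1: the plan's own figure.**
- Children per arm without clustering: 2 × (1.960 + 0.842)² / 0.2² = 392.4.
- Design effect: 1 + 29 × 0.05 + 30 × 0.01 = 2.75.
- Schools per arm: 392.4 × 2.75 / 60 = 17.99, so 18; 36 × 60 = 2160. The figure reproduces.
- Variance of a school mean: 0.01 + 0.04/2 + 0.95/60 = 0.0458. SE of the arm difference: √(2 × 0.0458/18) = 0.0714.
- Power is 0.800 on a normal test and 0.777 on a t-test with 34 df. This small difference has nothing to do with grade.

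**Step 2: the true precision.** Both bands sit equally in every school, so g is the same constant in every school mean and drops out of the arm difference. The true sampling SD is 0.071 for every g.

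**Step 3: the standard error if grade is random only.** On the scale of grade-band means, the expected mean squares are:
- between schools: 2 × 0.01 + 0.04 + 0.95/30 = 0.0917;
- between bands within schools: 0.04 + 0.95/30 + g²/2 = 0.0717 + g²/2.

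The second overtakes the first when g²/2 exceeds 0.02, that is when g exceeds 0.2 SD. The school variance estimate then tends to its zero bound and the model pools the two mean squares. At g = 0.5:
- between bands: 0.0717 + 0.125 = 0.1967;
- pooled: (34 × 0.0917 + 36 × 0.1967)/70 = 0.1457;
- SE: √(0.1457/18) = 0.090, against 0.072 on average with grade band fixed.

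**Step 4: power at a single visit.** Simulated balanced trials, non-negative variance estimates, t-test on 34 df:

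| Assumed gap g (SD) | Grade band fixed | Grade random only |
|---|---|---|
| 0.25 | about 77% | about 74% |
| 0.5 | about 77% | about 60% |
| 0.75 | about 77% | about 36% |

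At g = 0.2 the school variance is truncated in about half of trials, the mean SE is 0.073 and the power loss is about one percentage point. At g = 0.5 truncation occurs in more than 99% of trials and the type I error falls to about 1%.

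**Step 5: the change-over-time contrast of Section 11.2.5.** A gap that is the same at both visits drops out of each child's change. With an assumed between-visit correlation of 0.5 at every level, the change has the same variance components, since 2 × (1 − 0.5) = 1. The random-only analysis then has 77% power and SE 0.072 at constant gaps of 0, 0.5 and 1.0 SD. If the gap narrows from 0.5 to 0.3 SD, power is still about 77% with SE 0.0735. Only a grade difference in change well above 0.2 SD would cost power.

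**The case against.** The strongest reply has four parts.

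- **The text does not say random only.** It calls grades stratified units and draws them in order to adjust for age. Naming a hierarchy describes the clustering and need not list the fixed effects. Section 11.2.5 also allows analysis of covariance with unlisted covariates. This stands: a random-only fit is one literal reading, not a stated decision.
- **Fixed effects belong in the analysis plan.** True of a bare covariate list. Here, however, Section 11.2.3 gives both a purpose, adjusting for age, and a model built for it, and that model as described does not serve the purpose. The stated model can therefore be improved on its own terms.
- **The stated analysis is of change, where a constant gap costs nothing.** This stands for that contrast and limits the point considerably. It does not remove it: Section 11.1 compares the arms at 6 months, the sizing is for a single contrast, and adjustment for baseline can leave part of the gap in place.
- **Even at one visit the loss is conditional.** It needs a gap clearly above 0.2 SD and variance estimates held at zero or above. Without that bound, or with an analysis of school means, the SE stays at 0.071 and normal-test power at 0.80 for every gap. This also stands.

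A reader might infer that the planned 0.8 power is lost or that the trial is too small. The documents support neither. They give no age gap, the sample size reproduces, and the loss depends on a particular way of fitting the model.

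**Conclusion.** The point holds as one of model specification. Two fixed grade bands present in every school should not be represented by a nested level-2 unit alone, and no section names a grade-band term. If grade were fitted as random only, a 6-month contrast could fall from about 77% power to about 74%, 60% or 36% at gaps of 0.25, 0.5 or 0.75 SD. Those gaps are assumptions, and the figures also rest on non-negative variance estimates and the plan's own correlations. At gaps below about 0.2 SD, and for a constant gap in the change analysis, there is no material loss.

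The effect estimate stays unbiased. Any error is towards a conservative test, so the risk is a missed effect and not a false positive.

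**What to change.** State in Section 11.2.5 that grade band (Primary 1-3 versus Primary 4-6) enters the outcome models as a fixed effect with its interaction with time, alongside random effects for school and grade-within-school. The main effect removes the gap in level from the level-2 variance; the interaction with time does the same for a grade difference in change.

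The cost is one sentence. Grade band is known for every child from the sampling, no further data are needed, and the number of schools and children does not change. Power at a single visit is then about 77% on a t-test whatever the gap.
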